### Secondary hypotheses

MBSR would be an intervention modal with a long-term effect. We predict that at 1-year follow-up, the MBSR group would still show improvements in mental health, QOL, and medication treatment compliance, compared with its baseline levels.

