### Primary hypotheses

Participants in MBSR would show improvements in mental health, QOL, and medication treatment compliance, relative to control subjects. We predict that MBSR would help reduce psychological distress and increase patients’ ability to monitor negative cognitions and thereby decrease stress.The levels of mindfulness would increase over the course of the 8-week MBSR program, serving as a mediator to positive changes in mental health, QOL, and medication treatment compliance.

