#### Usual care regimen

Subjects randomized to the waitlisted control group will receive no formal intervention, but will continue to have standard post-treatment clinic visits according to their treatment plans. Additionally, to avoid possible overlap (contamination) with components of the MBSR program, the investigators will specifically ask subjects in the waitlisted control group not to start mindfulness-based practice during the study period.

MBSR intervention will be offered to each usual care subject after 6 months follow-up. They will be provided with a brief orientation to MBSR (BC), a manual on the program, and a 2-month practice class after post-assessment.

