#### Implementation

Following completion of their hospital treatment, BC survivors return home. As part of the newly launched cancer registry system, each community health service center (CHSC) in Shanghai collects BC survivors’ detail information in order to ensure follow-up and to analyze mortality and morbidity rates. Based on the patient lists from CHSC, we will contact these BC survivors directly to recruit potential participants. All participants who are willing to attend this trial will be requested to submit a signed informed consent. After that, all participants who provide an informed consent will then complete a baseline questionnaire for psychometric assessment (Time 0), with the help from investigators. Information about demographic background and health status will also be collected and later verified by a review of hospital charts.

The immediate intervention group will start the program within 2 weeks of randomization. Two certified MBSR psychotherapists will be hired to implement a standard MBSR intervention. Members of the research team will attend each MBSR session to ensure that intervention standards are met.

All subjects will be reassessed after the intervention group completes half of the program (4 weeks into the intervention, Time 1), 8 weeks later (Time 2), and at 6 (Time 3) and 12 months (Time 4) from the beginning of the intervention. Participants in the control group will be given the opportunity to complete the MBSR program after 6 months follow-up. Eight investigators will be in charge of these follow-ups by telephone.

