### Statistical methods

We will compare the outcome variables (SDS, SAS, MAAS, Quality of Life Index, and MMAS) between the two groups using the χ^2^ test for categorical variables and Student t or Wilcoxon tests for continuous variables. Analysis of covariance (ANCOVA) will be conducted to assess whether MBSR is related to changes between baseline and after 8 weeks of intervention in relation to psychological status, QOL, and compliance behaviors.We will use a structural equation model [45] to examine the intervening role of mindfulness enhancement on improving mental health, QOL, and compliance with medical treatment. Mediation analysis, as implemented in MPlus 7.11, will be used to analyze the causal pathway from MBSR intervention to health outcomes through mindfulness enhancement.We will use a random-effects repeated measures analysis [46] to examine the impact of MBSR intervention on health outcomes, compliance behavior, adjusting for confounding variables (age, education, household income, occupation, previous cancer history, and household registration status: Shanghai vs. non-Shanghai). The repeated measure analysis approach accounts for the same individual’s different outcome measures across different points in time without assuming either linear or curvilinear growth pattern. Cronbach alpha’s will be computed to determine the internal consistency of our outcome measures. Using this approach (as implemented by the PROC MIXED and PROC GLIMMIX modules in SAS 9.0), we have published an article analyzing a famous randomized controlled trial of lung cancer screening, which shows a behavioral differential between the two trial arms [47].

The relationship between methods used for each hypothesis is shown in Table 1.

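### The long-term effect of MBSR is tested only against the MBSR arm's own baseline, and no untreated control remains at 12 months, so a lasting change cannot be attributed to MBSR

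*Protocol article*

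**What the plan says.** The Secondary hypotheses section opens with a causal statement, "MBSR would be an intervention modal with a long-term effect", and then gives the testable prediction: "at 1-year follow-up, the MBSR group would still show improvements in mental health, QOL, and medication treatment compliance, compared with its baseline levels". The comparator is the arm's own baseline. The first primary hypothesis is framed differently: "Participants in MBSR would show improvements in mental health, QOL, and medication treatment compliance, relative to control subjects".

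On the control arm, Usual care regimen states: "MBSR intervention will be offered to each usual care subject after 6 months follow-up". It describes the offer as including "a 2-month practice class after post-assessment". Implementation repeats the timing: "Participants in the control group will be given the opportunity to complete the MBSR program after 6 months follow-up". Implementation also schedules all subjects for assessment at 4 weeks (Time 1), 8 weeks (Time 2), 6 months (Time 3) and 12 months (Time 4).

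Table 1 assigns the secondary hypothesis to Method 3. Statistical methods describes that method as follows: "We will use a random-effects repeated measures analysis [46] to examine the impact of MBSR intervention on health outcomes". It adds that no linear or curvilinear growth shape is assumed. It does not say that one effect is averaged over visits. The ANCOVA for the first primary hypothesis covers baseline to 8 weeks.

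**The concern.** A claim that an intervention has a lasting effect needs a concurrent comparison, because people change over a year for other reasons. The protocol gives several such reasons:

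- Women enter within 2 years of diagnosis and while on adjuvant therapy, so their symptoms may shift as treatment and recovery proceed.
- The baseline questionnaire is completed with help from investigators, whereas for later visits "Eight investigators will be in charge of these follow-ups by telephone". The mode of the baseline assessment is not stated, so a mode effect is possible but not certain.
- The Discussion accepts that women without early gain may leave, which would favour the intervention among those who stay.

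A single-arm comparison with baseline cannot separate any of these from MBSR. The other arm cannot help at 12 months. Its 2-month class can be finished between Time 3 and Time 4, so the arm contrast at Time 4 compares an early with a late offer of MBSR. The Discussion names spillover and attrition as threats to validity, but not this planned crossover.

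The claim matters to the authors' own case. The Background faults earlier work for short follow-up and for lacking evidence that effects last.

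**Working it through.** **Inputs from the protocol.** Sample size gives 195 per group, 390 in total, and 429 after allowing for 10% attrition (390 × 1.10 = 429). The 195 itself cannot be reproduced, because the SD, alpha, power and correlation are not stated. It is used here only as the number analysed per arm; 429 × 0.9 = 386, or 193 per arm, is close to it.

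**Assumptions, not in the protocol.** Natural improvement over a year of 0.1, 0.2 or 0.3 SD; correlation ρ between baseline and 12 months of 0.3 to 0.7; two-sided 5% test.

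**Step 1: within-arm test when MBSR has no effect.** In SD units the standard error of the mean change is √(2(1 − ρ)/n). With ρ = 0.5 and n = 195 this is √(1/195) = 0.0716. For a natural improvement of 0.2 SD, z = 0.2/0.0716 = 2.79, and the chance of significance is Φ(2.79 − 1.96) = 0.80. All cases:

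| Natural improvement | ρ = 0.3 | ρ = 0.5 | ρ = 0.7 |
|---|---|---|---|
| 0.1 SD | 22% | 29% | 44% |
| 0.2 SD | 66% | 80% | 95% |
| 0.3 SD | 94% | 99% | 100% |

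**Step 2: which between-arm contrasts the crossover touches.** Times 1, 2 and 3 precede the offer of MBSR to the waitlist, so contrasts at those visits are intact. So is the 8-week ANCOVA. Only a contrast at Time 4, or one that averages over Time 4, is affected.

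**Step 3: size of the dilution if Time 4 is pooled.** Assume a constant effect at Times 1 to 3, and let k be the fraction by which the waitlist catches up at Time 4. The average over four visits is (3 + (1 − k))/4 of the true effect. For power, assume compound symmetry with ρ = 0.5 and calibrate to 80% for the mean of the three visits before crossover, at 195 per arm. The variance factor for the mean of r visits is (1 + (r − 1)ρ)/r, which is 0.667 for three visits and 0.625 for four.

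| Catch-up k | Share of true effect | Power (from 80%) |
|---|---|---|
| 25% | 94% | 77% |
| 50% | 88% | 72% |
| 75% | 81% | 65% |
| 100% | 75% | 58% |

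Check of the last row: 0.75 × √(0.667/0.625) = 0.775; 0.775 × (1.96 + 0.84) = 2.17; Φ(2.17 − 1.96) = 0.58.

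**The case against.** The strongest reply is that the protocol asks a modest question and answers it. The stated prediction is improvement over the arm's own baseline, 12-month data in that arm test exactly this, and the wording suits a design whose controls have crossed over by then. This stands as far as it goes. A reader might infer that the 12-month data cannot answer the secondary hypothesis at all, but the literal prediction is testable. What cannot follow from it is the causal sentence that introduces it.

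A reader might also infer that the trial's efficacy estimate is diluted by the crossover. The protocol does not support that. The first primary hypothesis rests on bivariate tests and an ANCOVA ending at 8 weeks. Method 3 specifies no pooling over visits, and its freedom from a growth shape is compatible with visit-specific estimates. Sample size also speaks of three follow-ups, and exactly three precede crossover. Details of the model may properly sit in an analysis plan that is not shown.

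The drift is assumed as well. The Background says distress may persist after treatment. If women worsened naturally, the within-arm test would be biased against MBSR. The figures in Step 1 therefore show how easily the test could mislead, not that it will.

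Finally, the instruction to controls not to begin mindfulness practice while the study is running sits awkwardly with the offer after 6 months. The Discussion largely clears this up by saying they are to start only when they receive the intervention. It is loose wording, not a design flaw.

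**Conclusion.** The concern holds for the causal reading of the secondary hypothesis. This is a stated rule, not a silence: the protocol claims a lasting effect, fixes an uncontrolled test for it, and offers the control arm MBSR before the visit at which the test is made. With no MBSR effect, the test could be passed with probability 22% to 44% for an assumed drift of 0.1 SD, 66% to 95% for 0.2 SD, and 94% to 100% for 0.3 SD, over correlations of 0.3 to 0.7. Drift and correlation are assumptions throughout.

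Dilution of a repeated-measures arm effect, to between 94% and 75% of its true value, is conditional on pooling Time 4 and on 25% to 100% catch-up by women who are only offered the programme. The severity is should-fix: a secondary hypothesis is affected and the primary analysis is not.

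**What to change.** - State the causal long-term hypothesis as the between-arm difference at 6 months (Time 3), the last assessment before crossover. These data are already to be collected.
- Estimate the arm contrasts in Method 3 with group-by-visit terms, or from visits through Time 3 only.
- Keep 12 months as a description of maintenance in the immediate arm, with no causal claim. Label the waitlist's 12-month data as coming from women who have been offered MBSR.
- Reconcile the instruction to controls in Usual care regimen with the offer of MBSR after 6 months in the same section and in Implementation.

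The change is to wording and analysis only, and Trial status says the trial had not begun. The real cost is that the controlled long-term claim reaches 6 months, not 12; the design as written supports no more. The one-year maintenance question survives as a descriptive one.

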## Methods/Design

In this study, a randomized, waitlist controlled trial design will be used. The clinical trial registry number is ChiCTR-IOR-14005390.

### Setting and participants

Shanghai will be selected as the site of the study because it has been characterized by a high incidence of BC in China in recent years [35]. Participants in low-income households will be recruited from about 10 different communities from two of Shanghai’s poorer districts: Yangpu (characterized by an inner-city urban poor population of Shanghai origin) and Minhang (characterized by a migrant worker population).

Inclusion criteria are (1) female, (2) with a history of stage 0, I, II, or III BC, (3) within 2 years from the date of BC diagnosis, (4) currently under at least one adjuvant therapy.

Exclusion criteria are (1) current treatment for recurrent BC, (2) a history of schizophrenia or schizo-affective disorder [24], and (3) current alcohol or drug abuse.

### Intervention

#### MBSR intervention

Subjects assigned to the MBSR intervention group will receive weekly 2-hour sessions conducted by a psychologist certified and trained in MBSR. Class sizes may range from 20 to 30, with 8–10 groups in total. All sessions will be standardized and will follow the training manual to be developed to maintain consistency in the program. A trained psychologist will deliver the intervention. In addition, an observer will monitor the weekly sessions for inter-group consistency by recording the timing and other aspects of the intervention, and the quality of each session will be assessed in a qualitative post-observation report. Subjects will receive a training manual to support home practice of various forms of meditations (sitting meditation, body scan, and walking meditation) and gentle yoga. The training manual included weekly objectives, exercises, and program content related to the content identified below. In addition, the manual will include a daily diary for recording practice activities at home.

Based on Kabat-Zinn et al.’s MBSR program [22], this intervention will be an 8-week program adapted for the Chinese context, particularly for women in poorer socioeconomic situations. The objective of the intervention is to train participants to reduce their level of stress by self-regulating arousal to stressful circumstances or symptoms. At the beginning of each week, time will be provided for participants to discuss their experience, thus enhancing group interactions. More specifically, during week 1, participants will be given an overview of the intervention to establish a learning contract and to learn initial meditation and body scan procedures. In week 2, participants will learn visualization and will be introduced to sitting meditation with awareness of breathing as the primary object of attention. During weeks 3 and 4, participants will gain an understanding of one’s reaction to a pleasant event, body scan with response to stress, and introduction of yoga postures. Week 5 will instead provide participants with an understanding of their reaction to unpleasant rather than pleasant events. During weeks 6 and 7, participants will expand their field of awareness to allow for modification of stress-inducing patterns, and continue to monitor their awareness to allow these through techniques such as mountain meditation and/or lake meditation; awareness will be expanded to include objects such as bodily sensations, sounds, thoughts, and feelings. Finally, in week 8, participants will be encouraged to internalize practice sessions and develop a pattern for themselves. Participants will be told that week 8 is the first week of being on their own and to develop a lifetime program with the emphasis that meditation is a means to access wellness.

This modified intervention provides for management of specific emotional/psychological symptoms (anxiety, depression, and fear of recurrence) and physical symptoms, such as pain and sleeplessness. Through the use of meditation practices (sitting meditation, body scan, and walking meditation) and yoga, subjects are taught to increase awareness of their thoughts and feelings and to observe their emotional and physical responses during stressful situations. Through the process of mindfulness attention, subjects will take an active role in regulating their stress and managing symptoms and emotions, thus enabling them to cope better with the distress of having cancer. Administratively, the intervention will have three specific components: (1) educational material related to relaxation, meditation, and mind-body connection; (2) practice of meditation in group meetings and homework assignments; and (3) discussion among group members about barriers to practicing meditation, application of mindfulness in daily situations, and group support.

Throughout the 8-week MBSR program, all subjects will be requested to formally meditate (sitting, walking, and body scan exercises) 6 days per week. They will also be asked to informally practice 15–30 min per day, and this time will increase per week as participants become more experienced. Daily practice will be recorded in a diary each day. The total number of minutes/hours practiced over the 8-week program will also be recorded for analysis.

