### Sample size

Based upon an MBSR study among BC survivors where the intervention group had significantly better aggregated physical health outcome as measured by SF-36 (50.3 among MBSR subjects vs. 46.9 among the control group) [44], we used STATA 12.0’s power calculator to find that our two-group, three-follow-up design needs 195 participants for each of the two groups, i.e., 390 subjects in total. Assuming an attrition rate of 10 % (attrition rate here means the percent of people who drop out from the study due to moving away, death, etc.), we concluded that we need to recruit a sample of 429 BC survivors at baseline.

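### MBSR is given in 8–10 classes, but no stated between-group analysis includes class and no design effect is mentioned for the 195 per group; if outcomes correlate within a class, the planned standard errors are too small

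*Protocol article*

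**What the plan says.** Protocol article, MBSR intervention: the programme is taught weekly in groups. "Class sizes may range from 20 to 30", "with 8–10 groups in total". One of its three components is "discussion among group members about barriers to practicing meditation, application of mindfulness in daily situations, and group support". The Implementation section adds: "Two certified MBSR psychotherapists will be hired to implement a standard MBSR intervention".

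Usual care regimen: "Subjects randomized to the waitlisted control group will receive no formal intervention". They are offered their own MBSR class after the 6-month follow-up.

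Sample size: starting from a two-arm difference of 50.3 against 46.9, the article concludes that "our two-group, three-follow-up design needs 195 participants for each of the two groups". The only further allowance is 10% for attrition. No ICC, class size or design effect appears.

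Statistical methods: the arms are compared with chi-square, t or Wilcoxon tests, and "Analysis of covariance (ANCOVA) will be conducted to assess whether MBSR is related to changes between baseline and after 8 weeks of intervention". Mediation is examined with a structural equation model. A random-effects repeated-measures model is then fitted; the only dependence described for it is between one woman's measurements over time, and its adjustment list contains neither class nor therapist. Table 1 assigns Primary Hypothesis 1 to the bivariate tests and the ANCOVA.

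**The concern.** Women are allocated individually, but those in the MBSR arm are then treated in classes. They share sessions, an instructor and planned interaction with the same classmates. Each of these can make outcomes within a class more alike than outcomes in different classes. The waitlist arm has no such structure at 4 weeks, 8 weeks or 6 months, so the design is partially nested over that period.

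An analysis that treats all women as independent attributes too much information to the MBSR arm. Its confidence intervals are then too narrow and its p-values too small. This affects the 8-week comparison for Primary Hypothesis 1. A sample size that makes no allowance for clustering also gives a class-adjusted test less power than intended.

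**Working it through.** **The plan's own figure.** The difference is 50.3 − 46.9 = 3.4. The 195 per arm cannot be reproduced uniquely, because the SD, alpha, power and repeated-measures correlation are not stated. With a simple two-sided 5% comparison of means, 195 per arm corresponds to an SD of 11.98 at 80% power or 10.36 at 90%. Several repeated-measures combinations also come out near 195, and none needs a clustering term. Recruitment is 390 × 1.10 = 429, about 215 per arm.

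**Class size.** 195/10 = 19.5 and 195/8 = 24.4; 215/10 = 21.5 and 215/8 = 26.9. So about 20 to 27 women per class; m = 24 is used below. Both arms together would need about 390/25 = 15.6 to 429/25 = 17.2 classes, so the stated 8–10 groups fit the MBSR arm alone.

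**Assumptions not in the document.** ICC 0.01, 0.02, 0.05 and 0.10; two-sided alpha 5%; planned power 80%; equal class sizes; equal total variance in the two arms.

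**Formulae (through 6 months, clustering in the MBSR arm only).**
- Design effect in the MBSR arm: DE = 1 + (24 − 1) × ICC
- Variance of the difference relative to independence: VR = (DE + 1)/2
- True type I error of the planned unadjusted test: 2 × [1 − Φ(1.960/√VR)]
- Power of a class-adjusted test with 195 per arm: Φ(2.802/√VR − 1.960), where 2.802 = 1.960 + 0.842
- Power of the planned unadjusted test: Φ((2.802 − 1.960)/√VR)

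| ICC | DE | VR | √VR | Type I error, planned test | Power, class-adjusted test | Power, planned test |
|---|---|---|---|---|---|---|
| 0 | 1.00 | 1.000 | 1.000 | 5% | 80% | 80% |
| 0.01 | 1.23 | 1.115 | 1.056 | 6.3% | 76% | 79% |
| 0.02 | 1.46 | 1.230 | 1.109 | 7.7% | 71% | 78% |
| 0.05 | 2.15 | 1.575 | 1.255 | 11.8% | 61% | 75% |
| 0.10 | 3.30 | 2.150 | 1.466 | 18.1% | 48% | 72% |

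The type I error and class-adjusted power columns belong to different tests. The planned test keeps most of its apparent power because it rejects too often.

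**Check by simulation.** A t-test on 8 classes of 24 against 192 unclustered controls, 40,000 runs, rejected a true null in 4.9%, 6.3%, 7.8%, 11.9% and 17.6% of runs at ICC 0, 0.01, 0.02, 0.05 and 0.10.

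**Sensitivity to class size.** At ICC 0.05 the type I error is 10.7% with 20 per class and 13.6% with 30.

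**Size that would keep the intended power.** 195 × VR, with classes held at 24, gives 218, 240, 308 and 420 per arm at ICC 0.01, 0.02, 0.05 and 0.10.

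**The case against.** The strongest reply is that the harm is conditional. No ICC is given, and at 0.01 the type I error is only about 6%. The plan also takes steps that should limit variation between classes: standardized sessions, a common manual, an observer checking consistency, and research staff at each session. This stands in part. Such measures may lower the ICC, but they do not remove correlation that arises from group interaction, which is itself part of the treatment. The type I figures also describe a null in which the average effect is zero but classes still differ; the too-narrow intervals do not depend on that null.

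A second reply is that this is a condensed article, and the random terms of a mixed model are commonly left to an analysis plan that is not shown. That has some force for the repeated-measures model. It has less for the t, Wilcoxon and ANCOVA comparisons, which are stated outright as the methods for Primary Hypothesis 1. Likewise, since the inputs to the 195 are not shown, one can say that no design effect is mentioned, not that none was used.

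Three stronger readings are tempting, and the documents do not support them:
- That the type I error is certainly inflated. This needs an ICC above zero, which the documents neither give nor rule out.
- That the plan as written suffers both 18% type I error and 48% power. The first figure is for the planned unadjusted test, the second for a class-adjusted test that is not planned.
- That the full design effect applies to the comparison. Through 6 months only one arm is in classes, so the factor is (DE + 1)/2. Recruitment from about 10 communities is not the cause either, because allocation is by individual.

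**Conclusion.** The point holds as a conditional one. The stated between-group analyses leave out a feature of the design that the article itself describes, and whenever the within-class ICC is above zero their standard errors are too small. With about 24 women per class, the true type I error of a nominal 5% test runs from about 6% at ICC 0.01 to 18% at ICC 0.10. A valid class-adjusted test with 195 per arm would have about 76% down to 48% power, if the unstated target was 80%. At ICC 0 neither figure moves.

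The omission is plain from the text; its size rests on the assumed ICC. The power figures use a normal approximation, and with only 8–10 classes a small-sample correction would lower them somewhat further. The one-arm calculation applies through 6 months. It does not describe 12 months, when waitlisted women may also have attended classes, nor the secondary hypothesis, which compares the MBSR group with its own baseline.

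**What to change.** - Record a class identifier for every woman who attends, including waitlisted women in their later classes. Without it the correction may not be possible afterwards.
- Fit the 8-week ANCOVA and the repeated-measures model through 6 months as partially nested mixed models in the PROC MIXED already planned: a random class effect in the MBSR arm only, arm-specific residual variance and Kenward–Roger degrees of freedom.
- At 12 months, also model the waitlist arm's own classes; treating each waitlisted woman as her own unit no longer fits there.
- Account for class in the structural equation model, and say that clustered standard errors are approximate with 8–10 classes.
- Label the t, Wilcoxon and chi-square comparisons as descriptive. They need not be dropped.
- State the alpha and power behind the 195 per arm, and the power it gives over an assumed ICC range, so that the sponsor can decide whether that size is acceptable. Restating power does not restore it.

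The cost is one extra variable, some analysis wording and a paragraph on power, and the Trial status section says that the trial had not begun. The price is wider confidence intervals and a less favourable stated power. If the sponsor chose to keep the intended power, the larger numbers per arm shown in the working would add real recruitment cost.
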